### Retention of Study Participants

Contact information of the participants, alternative contact persons, and preferred times for making phone calls for safe contact will be collected in order to keep in touch with them. If a participant absconds from a scheduled session or follow-up, the intervention implementer will try to contact her over the phone and encourage her to attend all sessions and follow-ups. If the participant is still absconding or cannot be contacted over the phone, the intervention implementer will contact female community health volunteers to follow up with the participant personally or over the phone. Female community health volunteers properly informed by the intervention implementer will then personally visit the participant at home following ethical guidelines [25]. All ethical guidelines [25] described in detail in the *Ethical Considerations* section will be considered while following up with participants to continue and complete the intervention. However, participants will be clearly informed that they are free to withdraw from the trial at any time without giving reasons.

### Randomization and Blinding

From a sampling frame of 43 health care facilities available in Madhesh Province, a total of 24 (56%) facilities were selected based on the flow of women seeking various health-related services. The selection process involved randomization of health care facilities using a computer-generated random number table, ensuring a 1:1 ratio of intervention and control clusters (12, 50%, intervention and 12, 50%, control clusters). Each health care facility represents 1 cluster.

Participants visiting the intervention sites will be recruited into the intervention arm, while those visiting the control sites will be recruited into the control arm. To maintain blinding, both participants and health care facility staff will be completely unaware of the information pertaining to the 2 different arms, as well as the arm to which their respective health care facility belongs. However, it may not be possible to conceal this information from the study team responsible for the study design. Therefore, the study will be unmasked during data monitoring, evaluation, and analysis.

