### Procedure

Trained ANMs and nurses will be referred to as data collectors and intervention implementers, respectively. Their role throughout the study will be to approach women visiting health care facilities and screen them using a questionnaire for willingness to participate and eligibility. The study process is illustrated in Figure 3.

Data collectors will provide detailed information about the study to potential eligible participants and obtain written informed consent for a baseline assessment. Once consent is obtained, data collectors will conduct a baseline assessment. The baseline assessment will take about 30-45 minutes, which will be carried out in a separate room at the health care facilities. Participants will be made aware that refusal to participate will not have an impact on any type of support that they receive outside of the study. The detailed steps of study activities are listed in Table 2.

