#### Intervention Arm

After the baseline assessment, study participants will be referred by data collectors to intervention implementers, whose role is to deliver the intervention package once a week, with each session lasting around 90 minutes. The intervention package aims to prevent the recurrence of IPV/domestic violence and address psychological distress among participants. During each session, intervention implementers will administer the Psychological Outcome Profiles (PSYCHLOPS) form, a mental health and social functioning tool. Before-intervention PSYCHLOPS data will be collected in session 1, and during-intervention PSYCHLOPS data will be collected in sessions 2-5. At the end of each session, the intervention implementer will schedule the participant’s next session. The intervention implementers will guide and encourage the participants to develop personalized plans and strategies for managing their problems, create a safety plan, and fully use existing community organizations and social support.

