#### Other Outcomes

Health care providers will be asked to respond to questionnaires, such as the modified Physician Readiness to Manage Intimate Partner Violence Survey (PREMIS), the Mental Health Knowledge Schedule (MAKS), the Social Distance Scale, and the perceived dangerousness of mental health patients pre- and posttraining to assess the impact of training on the health care providers’ knowledge and attitude. Further, MAKS and the perceived dangerousness of mental health patients will be assessed during integrated multicomponent supervision (approximately 90 days posttraining). Exit interviews will be conducted among 180 participants by data collectors in the absence of intervention implementers after the completion of all 5 sessions in a separate room by adopting a mixed methods approach. This will help determine changes postintervention and any aspects that need to be changed. This will also help assess the satisfaction and acceptability of DeVI from the participant’s point of view.

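### The blinding statement cannot hold at intervention sites: facility nurses deliver DeVI, and the data collectors who refer women to it also collect the self-reported primary outcomes

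*Protocol article*

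**What the plan says.** Randomization and Blinding states that "both participants and health care facility staff will be completely unaware of the information pertaining to the 2 different arms", and extends this to the arm of their own facility. It concedes only that the team behind the study design may know the allocation, and concludes: "Therefore, the study will be unmasked during data monitoring, evaluation, and analysis".

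The same section fixes the arm by facility before any woman is enrolled: "Participants visiting the intervention sites will be recruited into the intervention arm", and correspondingly for control sites.

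Other sections describe who does what:

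- **Roles.** Procedure says: "Trained ANMs and nurses will be referred to as data collectors and intervention implementers, respectively".
- **Referral.** Under Intervention Arm, after baseline "study participants will be referred by data collectors to intervention implementers".
- **Exit interviews.** Other Outcomes says: "Exit interviews will be conducted among 180 participants by data collectors in the absence of intervention implementers after the completion of all 5 sessions".
- **Follow-up.** Table 2 assigns the 6-, 17- and 52-week assessments in both arms to data collectors.
- **Screening.** Procedure says of both roles together: "Their role throughout the study will be to approach women visiting health care facilities and screen them using a questionnaire". The Recruitment section also names both ANMs and nurses. Table 2 gives screening to data collectors only.

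**The concern.** The article claims a property that its own procedures rule out. This is a positive statement, not a detail left to a fuller protocol or an analysis plan.

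It matters because both primary outcomes, psychological distress and IPV/domestic violence, are what a woman tells a data collector. Entry also depends on what she tells the person screening her, since abuse in the past 12 months and a GHQ-12 score of at least 3 are self-reported. When the person asking knows the arm, two biases are possible: who is found and enrolled may differ between arms, and so may what is disclosed at follow-up. A reader who accepts the blinding statement would discount both, and the Limitations section mentions neither.

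**Working it through.** **Step 1. Test the claim group by group.**

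| Group | What the article says | Can they be unaware? |
|---|---|---|
| Implementers, intervention sites | 10-day training centred on DeVI (Training of the Study Team); deliver five weekly sessions of about 90 minutes (DeVI section, Table 2) | No |
| Data collectors, intervention sites | Refer women to implementers (Intervention Arm); hold exit interviews (Table 2, Other Outcomes); assess outcomes (Table 2) | No |
| Women, intervention sites | Given study details before baseline (Procedure); DeVI is the name used with participants (Background); attend five sessions | They know they receive DeVI; whether they know of a comparison arm is not stated |
| Women, control sites | Standard care and a booklet (Control Arm, Information Booklet) | Possibly unaware of another arm |
| Staff, control sites | Study Design and Setting counts 30 control-site workers among 63 trained to deliver DeVI; Training of the Study Team gives data collectors of both arms a 3-day data-collection course | Cannot be settled from the text |

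The claim fails for the first two groups. For intervention women it fails as regards knowing what they receive.

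**Step 2. Order of events.** The facility is allocated, then a woman is approached, screened, assessed at baseline and, at intervention sites, referred. The 6-week assessment falls one week after the intervention ends (Follow-up Assessments). The exit interview, after session 5, therefore precedes it by about a week at most.

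**Step 3. Who screens.** Recruitment and Procedure allow both roles; Table 2 allows one. Under the first reading, those who will deliver DeVI may help choose who enters.

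**Step 4. Size of a reporting bias (illustration).** The article gives no control-arm IPV risk and no reporting error, so both are assumed. Let p be the true risk, equal in both arms, and u the share of affected women in one arm who do not report. The spurious difference is p − p(1 − u) = p × u.

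- p = 50%, u = 5%: 0.50 × 0.05 = 2.5 points.
- p = 50%, u = 20%: 0.50 × 0.20 = 10 points.
- p = 30%: 1.5 to 6 points. p = 70%: 3.5 to 14 points.

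The Sample Size section plans on a 15-point reduction. At p = 50% the spurious difference is 2.5/15 = 17% to 10/15 = 67% of that target.

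**Step 5. Effect on the test (illustration).** Take 456 women per arm in clusters of 38 (both from the article), a reported risk of 0.5 to 0.7, an ICC of 0.01 to 0.05 (both assumed) and no true effect. Then n_eff = 456 / (1 + 37 × ICC), SE = √(2p(1 − p)/n_eff), and for a reporting shift b the rejection probability is Φ(b/SE − 1.96) + Φ(−b/SE − 1.96).

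- Example: p = 0.5, ICC = 0.05 gives n_eff = 456/2.85 = 160 and SE = √(0.5/160) = 0.056. With b = 0.05, b/SE = 0.89 and the probability is 0.145.
- Over the assumed range, b = 5 points gives about 15 to 29%, and b = 10 points about 43 to 80%, against a nominal 5%.

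**The case against.** **Roles are separated.** Data collectors and implementers are different people by definition, implementers are kept out of the exit interview, and data collectors make the follow-up assessments. A reader might infer that one group of staff does everything; the article does not say so. The separation does not rescue the blinding statement, because the data collector makes the referral herself.

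**Open-label for everyone?** A reader might infer this too, but the article does not establish it. Consent wording is not shown, the intervention's name is described as neutral, and control women could be kept unaware of a comparison. This part of the objection stands.

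**Enrolment of 269 against 309.** A reader might take this as selective recruitment already visible. It is not. Ignoring clustering, z = (309 − 269)/√578 = 1.66, p = 0.096; with assumed design effects of 1.5 to 2.7, p is 0.17 to 0.31. With a fixed 38 women per facility, an interim count may show pace only.

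**The bias could run either way.** DeVI teaches women about the cycle of violence and its staff are trained to build trust, so disclosure may rise in the intervention arm and hide a benefit. This stands. The illustration shows size, not direction.

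**Unmasked analysis is openly disclosed.** True, so it is no concealment. But the reason given does not support it: designers knowing the allocation does not require the analyst to know it. Nor is analyst masking the only level possible. Outcome collectors separate from the facility and from referral would be another.

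**Conclusion.** The blinding statement is wrong as written for implementers and data collectors at intervention sites, and for intervention women as regards what they receive. Whether control women know of another arm cannot be told from the article. Allocation before recruitment, entry by self-report and self-reported primary outcomes leave recruitment bias and differential reporting open, in either direction.

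Nothing in the article shows that either bias has occurred. The 2.5 to 10 points rest on an assumed 50% risk and an assumed 5 to 20% under-reporting in one arm; the false-positive rates rest on assumed risks and ICCs. They show only that modest differential reporting would be large against a 15-point target.

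**What to change.** 1. **Replace the blinding sentence.** Say that implementers, recruiters and outcome collectors are not masked and that intervention women know they receive DeVI. State what women in each arm are told about the other arm.
2. **Settle who screens.** Bring Recruitment and Procedure into line with Table 2, so that data collectors, not implementers, approach and screen, by the same procedure in both arms. Report numbers screened, eligible and consented, and baseline data, by facility and arm. If earlier logs do not exist, report screening from the date of the change.
3. **Mask the analyst.** Use coded arm labels until the primary models are run.
4. **Extend the Limitations section.** Name recruitment bias and reporting bias.

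Optionally, hold the exit interview after the 6-week questionnaires. This may reduce priming among the 180 women interviewed, but does not restore masking.

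The cost is wording, a screening log and coded labels, with no new staff. The stated design becomes less favourable. By 29 December 2022, 269 + 309 = 578 of 912 women (63%) were enrolled, so the screening change reaches at most about the last third. These steps make the masking status accurate and selection visible, but unmasked staff still collect the outcomes. Only collectors separate from facility and referral would change that, at the price of additional staff.

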### DeVI: An Integrated Multicomponent Intervention

This intervention is structured into 5 weekly sessions, where each session lasts for about 90 minutes. The first session includes general information about DeVI, components to understand the cycle of violence, and its potential health impacts. Following this, the second session focuses on common health problems caused by IPV, mental health consequences, the purpose of managing stress, and techniques for managing stress. The third session emphasizes on strategies to help women manage their situation and develop their own customized problem management strategies. This session aims to improve participants’ ability or skills to solve and manage practical problems that may be influenced by other factors or changed by conflict in the family or unsolvable problems, such as employment. These problems are managed considering the participants’ existing personal strengths, resources, or support. This is followed by exploring safety-planning behaviors and preparing a customized safety plan in the fourth session. The last session involves exploring social support and assisting participants in planning to strengthen the social support identified. The contents of DeVI are detailed in Table 1.

**Table 1 table1:** Contents of DeVI^a^.

Intervention session	Contents of PM+^b^ [16]	Additional components of DeVI
Session 1: understanding the muticomponent intervention	Introduction and confidentiality Before-intervention PSYCHLOPS^c^ assessment	General information about DeVI IPV^d^ and domestic violence, the cycle of violence, and its common impacts on health
Session 2: common consequences of IPV and domestic violence and managing stress	During-intervention PSYCHLOPS assessment and general review Purpose of managing stress Explanation and demonstration of some common stress management techniques Strategies to manage stress	Information about common health problems associated with IPV/domestic violence Details about the common mental health consequences of IPV/domestic violence Case of a women experiencing IPV/domestic violence
Session 3: managing problems	During-intervention PSYCHLOPS assessment and general review Strategy for managing problems and its usefulness Practice of the problem-managing strategy through a case example Application of the strategy in solving practical problems identified by participants Plan to solve the identified problems Practice of stress management techniques	Behavioral activation, during which participants will be encouraged to gradually re-engage with pleasant and task-oriented activities to improve mood and functionality
Session 4: development of a safety plan	During-intervention PSYCHLOPS assessment and general review	Safety behavior assessment Safety-planning behaviors applicable to the participants’ context Barriers to and facilitators of using safety behaviors Preparation of a safety plan in times of need Information about applying for legal protection orders Filing criminal charges
Session 5: strengthening social support and referrals	During-intervention PSYCHLOPS assessment and general review Available social support Assisting participant in making plans and approaches for strengthening social support identified	Distribution of an information booklet that details updated contact information or locally available organizations that offer different services to women experiencing IPV

^a^DeVI: Domestic Violence Intervention.

^b^PM+: Problem Management Plus.

^c^PSYCHLOPS: Psychological Outcome Profiles.

^d^IPV: intimate partner violence.

### Procedure

Trained ANMs and nurses will be referred to as data collectors and intervention implementers, respectively. Their role throughout the study will be to approach women visiting health care facilities and screen them using a questionnaire for willingness to participate and eligibility. The study process is illustrated in Figure 3.

Data collectors will provide detailed information about the study to potential eligible participants and obtain written informed consent for a baseline assessment. Once consent is obtained, data collectors will conduct a baseline assessment. The baseline assessment will take about 30-45 minutes, which will be carried out in a separate room at the health care facilities. Participants will be made aware that refusal to participate will not have an impact on any type of support that they receive outside of the study. The detailed steps of study activities are listed in Table 2.

**Figure 3 figure3:**
[figure not shown]
Flowchart of the study process.

**Table 2 table2:** Detailed steps of study activities at the cluster level.

Steps and arms		Timing	By whom	Determined by	Rationale	Outcome
**Screening**						
	Both intervention and control arms	N/A^a^	Data collectors	Data collectors	To screen eligible participants for the study. Data collectors will inform participants about the study and obtain written informed consent.	N/A
**Enrollment and baseline data collection**						
	Both intervention and control arms	N/A	Data collectors	Data collectors	Baseline data collection will help track the impact of the intervention.	Assessment of primary outcomes (psychological distress and occurrence of IPV^b^/domestic violence) at baseline
**DeVI^c^**						
	Intervention arm only	90 minutes/week for 5 weeks	Intervention implementers	Intervention implementers	To implement the intended intervention in the intervention arm.	N/A
	Intervention arm only	After session 5	Data collectors	Data collectors	To assess participants’ perception toward the intervention.	Exit interview to assess participants’ satisfaction and suggestions
**Follow-up**						
	Both intervention and control arms	6, 17, and 52 weeks after baseline in both arms	Data collectors	Data collectors	To compare baseline data with follow-up data between control and intervention arms.	Impact of the intervention on primary outcomes and secondary outcomes, such as a change in social support
**Follow-up of absconding participants**						
	Both intervention and control arm	N/A	Female community health volunteers	Data collectors and intervention implementers	Female community health volunteers to contact absconding participants over the phone or in person to reduce the attrition rate as much as possible.	Assessment of other outcomes, such as reasons for absconding

^a^N/A: not applicable.

^b^IPV: intimate partner violence.

^c^DeVI: Domestic Violence Intervention.

#### Intervention Arm

After the baseline assessment, study participants will be referred by data collectors to intervention implementers, whose role is to deliver the intervention package once a week, with each session lasting around 90 minutes. The intervention package aims to prevent the recurrence of IPV/domestic violence and address psychological distress among participants. During each session, intervention implementers will administer the Psychological Outcome Profiles (PSYCHLOPS) form, a mental health and social functioning tool. Before-intervention PSYCHLOPS data will be collected in session 1, and during-intervention PSYCHLOPS data will be collected in sessions 2-5. At the end of each session, the intervention implementer will schedule the participant’s next session. The intervention implementers will guide and encourage the participants to develop personalized plans and strategies for managing their problems, create a safety plan, and fully use existing community organizations and social support.

#### Enhanced Standard Care or the Control Arm

Control arm participants will receive standard care provided by the local health care facilities, depending on what they seek care for, and they will also receive an information booklet. Any participant with severe psychological distress or at risk for suicide will immediately be referred to a psychiatrist. Psychiatrists can provide remote counselling over the phone to the participant and, if necessary, also visit the participant in person. The study team will arrange the time, schedule, and consultation fees for the psychiatrist in both study arms, particularly for severe cases involving suicidal ideation identified during screening. Further, if the participant prefers to visit a psychiatrist herself, she will be provided with the travel cost.

#### Information Booklet

Both intervention and control arms will receive an information booklet that contains updated contact information for referral services in the study area. Further, they will receive information about the psychological distress resulting from IPV/ domestic violence and available services in the local context for psychological and legal support. Ahead of the study, the study team contacted and coordinated with concerned NGOs or community organizations working in the field of prevention of violence against women or management of mental health problems in the study area to ensure that women have safe places to visit in case of an emergency or difficulty.

#### Follow-up Assessments

Follow-up surveys will be conducted at 3 time points: 6 weeks after baseline assessment (ie, 1 week postintervention), 17 weeks after baseline assessment (ie, 12 weeks postintervention), and 52 weeks after baseline assessment (ie, 47 weeks postintervention). The data collection tools for follow-up will be similar to those for baseline assessments. However, in the last follow-up, participants will be asked questions and will be expected to contribute to the assessment of any sustained effects of DeVI on the prevention of revictimization and improvement in coping strategies against IPV. An exit interview will be conducted after intervention session 5.

IDIs will be conducted with health care providers from the intervention arm during or after the intervention to explore their experiences and perspectives of DeVI and program implementation. Health workers will be mobilized to identify suitable participants in the community, and those who provide written informed consent will be contacted for confidential interviews, preferably at the health care facility, both during and after the intervention.

